### Statistics

#### Statistical tests

All statistical analyses will be performed using IBM SPSS software using intention-to-treat and per protocol analyses. Nominal data will be described by frequencies and percentages, and correlations will be analyzed using the chi-square test; continuous data will be expressed as mean ± standard deviation or median (range), and analyzed using Student’s *t* test or the Mann-Whitney *U* test depending on the normality of the data. The primary outcome, the percentage of miscarriage before 20 weeks of gestation, will be analyzed with the chi-square test. Subgroup analysis for the primary outcome will be done with regard to gravida, gestation at presentation, presence of subchorionic hematoma and after exclusion of those with an abnormal karotype in the abortus. The secondary outcomes will be compared between the treatment group and the control group by the chi-square test. Logistic regression analysis will be performed to find out the independent predictive factors for miscarriage. A *p* value <0.05 will be considered as statistically significant.

Every attempt will be made to collect full follow-up data on all women (unless a woman withdraws consent for follow-up data collection). In particular, women will be followed up even after protocol violation. It is thus anticipated that missing data will be minimal. Women with missing primary outcome data will not be included in the primary analysis. This presents a risk of bias, and secondary sensitivity analyses will be undertaken to assess the possible impact of the risk, including the assumption that all women lost to follow-up have miscarriages before 20 weeks. Other sensitivity analyses will involve simulating missing responses using a multiple imputation.

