## Methods

### Trial design (Table 1)

This is a double-blind, randomized controlled trial. The study will be conducted in two public hospitals in Hong Kong: Queen Mary Hospital and Kwong Wah Hospital. Queen Mary Hospital is the affiliated hospital of the Faculty of Medicine, the University of Hong Kong. An ethics approval has been obtained from the Institutional Review Board of the University of Hong Kong/Hospital Authority Hong Kong West Cluster (Ref number: UW 13-292). Written informed consent will be sought from subjects at the time of recruitment, including consents for collection of tissue mass and for further chromosomal and molecular studies. The clinical trial protocol also follows the SPIRIT 2013 checklist (Additional file 1).

**Table 1 Tab1:** The schedule of enrollment, interventions and assessments^a^

	Study period					
	Enrollment	Allocation	Post-allocation			Close-out
Timepoint^b^	3/2016 until present	0	Weekly until 12 completed gestational weeks or 1 week after bleeding has stopped, whichever is longer	20 weeks	Until delivery	24th month
Enrollment:						
Eligibility screen	X					
Informed consent	X					
(List other procedures)						
Allocation		X				
Interventions:						
(Dydrogesterone)			X			
(Placebo)			X			
(List other study groups)						
Assessments:						
Pelvic scan, serum hCG and progesterone			X			
(Primary outcome)				X		
(Secondary outcomes)					X	X

^a^Recommended content can be displayed using various schematic formats. See *SPIRIT 2013 Explanation and Elaboration* for examples from protocols [27]

^b^List of specific timepoints in this row

*hCG* human chorionic gonadotropin

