#### Inclusion criteria

Age of women from 18 to 40 years at the time of recruitment (not beyond 40th birthday)Absence of fever (temperature ≥38.5 °C)Gestation less than twelve completed weeks as defined by pelvic ultrasoundPresence of intrauterine gestational sac(s) if a urinary pregnancy test is first positive within the past 2 weeksPresence of intrauterine fetus(es) with positive fetal heart pulsation or presence of intrauterine fetus(es) with crown-rump length of less than 7 mm and no fetal pulsation on pelvic scanning

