In order to increase the generalizability of our results, we do not exclude subjects with multiple pregnancy and uterine anomaly, and we also include pregnancy of uncertain viability. However, this decision may potentially increase the heterogenicity of the results and this may be one of the limitations of the study.

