#### Sample size estimation

Based on the two previous studies [11, 12], with the pooled miscarriage rate in the progestogen group and control group being 27/182 (14.8 %) versus 42/155 (27.1 %), respectively, a sample size of 171 per group is needed to achieve a power of 80 % with a type I error of 0.05. To allow for drop out, we plan to recruit 400 subjects in total with 200 patients in each arm.

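### The primary chi-square test is valid, but it leaves unused the fetal heart status and gestation recorded at entry; prespecified adjustment is a cheap gain in power

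*Protocol article*

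**What the plan says.** All of these points are in the protocol article.

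- **Primary test** (Statistical tests): "The primary outcome, the percentage of miscarriage before 20 weeks of gestation, will be analyzed with the chi-square test". The threshold is "A *p* value <0.05 will be considered as statistically significant". Logistic regression appears in the same section, but its stated job is to identify predictors of miscarriage. It is not described as a treatment comparison.
- **Subgroups** (Statistical tests): gravidity, gestation at presentation, subchorionic hematoma, and exclusion of abnormal karyotypes. Fetal heart status is not listed.
- **Who enters** (Inclusion criteria): women with a beating fetal heart, women with a fetus of "crown-rump length of less than 7 mm and no fetal pulsation on pelvic scanning", and women with only a gestational sac if the pregnancy test first became positive in the preceding two weeks. Selection and withdrawal of subjects gives an entry range of 5 to 12 weeks.
- **The authors' own view of this mix** (Treatment of subjects, repeated in the Discussion): "we also include pregnancy of uncertain viability. However, this decision may potentially increase the heterogenicity of the results", which they call a possible limitation.
- **What is recorded at entry** (Treatment of subjects): age, estimated gestational age and ultrasound findings, among others.
- **Allocation** (Treatment of subjects): 1:1 in blocks of 10, with no stratification factor named. Two hospitals take part.
- **Size** (Sample size estimation): "a sample size of 171 per group is needed to achieve a power of 80 % with a type I error of 0.05", and then "To allow for drop out, we plan to recruit 400 subjects in total with 200 patients in each arm".

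**The concern.** A woman whose scan shows a beating heart and a woman with an empty sac or a small fetus without pulsation plausibly have very different chances of miscarriage. The protocol recognises this, has the information for each woman at entry, and then fixes a primary test that does not use it.

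Two things are at stake. If heart status predicts outcome strongly, the unadjusted test gives up power that could be had without recruiting anyone. And since no stratification is described, the arms may by chance differ in their share of uncertain pregnancies, which makes the unadjusted estimate less precise and harder to defend when the baseline table is read.

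**Working it through.** **1. Reproduce the stated sample size.** Inputs from Sample size estimation: p₁ = 0.148, p₂ = 0.271, α = 0.05 (taken as two-sided, which reproduces the figure), power 80%. With p̄ = (0.148 + 0.271)/2 = 0.2095:

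n = [1.96·√(2p̄(1−p̄)) + 0.8416·√(p₁(1−p₁) + p₂(1−p₂))]² / (p₂−p₁)²
= [1.96 × 0.5755 + 0.8416 × 0.5689]² / 0.123² = 170.7, so 171 per group.

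This agrees with the protocol. The raw fractions 27/182 and 42/155 give 172. Power by formula is 80.1% at 171 per arm and 85.9% at 200 per arm. The calculation is for an unadjusted comparison of two proportions, so the planned test and the sample size agree.

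**2. Set up the adjusted comparison.** The documents give neither the share of women without heart activity (s) nor their miscarriage risk (r₁). Both are assumptions here: s = 10-30%, control risk r₁ = 40-70%. The control risk in women with heart activity, r₀, is then fixed by the protocol's overall control rate:

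r₀ = (0.271 − s·r₁)/(1 − s)

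Example, s = 0.30 and r₁ = 0.60: r₀ = (0.271 − 0.180)/0.70 = 0.130.

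A common odds ratio is chosen so that the treated arm averages 14.8%. In the example it is 0.387. Treated risks become 1.5 × 0.387 = 0.580 in odds, or 36.7%, and (0.130/0.870) × 0.387 = 0.058 in odds, or 5.5%. Check: 0.30 × 0.367 + 0.70 × 0.055 = 0.148.

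**3. Simulate.** There were 40,000 trials per scenario with 171 per arm. The comparison is the Pearson chi-square test against a Mantel-Haenszel test stratified by heart status, the score-test counterpart of logistic regression with treatment and that factor. Simulation error is about √(0.8 × 0.2/40,000) = 0.2 point.

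| Share without heart activity | Control risk, not seen vs seen | Chi-square | Adjusted | Gain (points, approx.) |
|---|---|---|---|---|
| 10% | 40% vs 26% | 81% | 81% | 0 |
| 20% | 50% vs 21% | 81% | 83% | 2 |
| 20% | 60% vs 19% | 81% | 86% | 5 |
| 20% | 70% vs 16% | 81% | 89% | 8 |
| 30% | 50% vs 17% | 81% | 84% | 3 |
| 30% | 60% vs 13% | 80% | 88% | 8 |
| 30% | 70% vs 9% | 81% | 93% | 12 |

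Type I error was near 5% for both tests. With all 200 per arm evaluable, chi-square power is about 86%, and the 30%/60% scenario rises to about 93%.

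**4. Chance imbalance.** With s = 0.30 and 171 per arm, the 95% range for the between-arm difference in share is ±1.96·√(2 × 0.3 × 0.7/171) = ±9.7 points. Multiplied by the control-arm risk gap of 0.60 − 0.13 = 0.47, this moves the unadjusted risk difference by up to about ±4.6 points, against a planned effect of 27.1 − 14.8 = 12.3.

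**5. Hospital.** With two equal hospitals and risks 10 points apart, the variance explained is 0.25 × 0.10²/(0.271 × 0.729) = 1.3%. Power at 171 per arm goes from 79.8% to 80.3% (formula, raw fractions).

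**6. Room for covariates.** Expected events in 400 women: 200 × (0.271 + 0.148) ≈ 84. In 171 per arm: 171 × 0.419 ≈ 72. Treatment, three-level heart status, linear gestation and linear age use five parameters, or about 14 to 17 events per parameter.

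**The case against.** The case for leaving the plan alone is respectable. The chi-square test is valid after randomization, its type I error already allows for chance imbalance, and it matches the sample-size calculation. The gain depends on figures that the documents do not contain and disappears if few women lack heart activity or the factor is weak. The check used one binary factor, not the full model proposed. Heart status and gestation overlap, because entry without a heartbeat is confined to very early pregnancies. All of that stands. It makes this an efficiency point with a conditional size.

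It does not remove the point. The choice of primary test is stated in the protocol, not left open, and logistic regression is given a different job.

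A reader might be tempted to go further in four ways that the documents do not support:

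- **That the planned test is wrong or underpowered.** At the protocol's own rates it has the 80% claimed.
- **That the analysis must account for hospital.** No stratification by hospital is stated, and adjustment adds about half a point of power at most.
- **That adjustment removes most of the unexplained variation.** In the 30%/60% example heart status explains 0.21 × 0.47²/(0.271 × 0.729) ≈ 23% of control-arm outcome variance, and about 40% at the extreme.
- **That the lack of a stated effect size or interval is a defect.** Naming a test does not exclude reporting either, and a full plan may specify them.

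**Conclusion.** The point holds as a free or cheap improvement, not as a correction of an error. The protocol identifies mixed viability as a weakness, has the relevant baseline information, and fixes a primary analysis that leaves it unused. At 27.1% versus 14.8% with 171 per arm, adjustment for heart status lifts power from about 80-81% to about 81-93%, a gain of about 0 to 12 points.

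That range rests on three assumptions: 10-30% of women without heart activity, a 40-70% control risk among them, and a common odds ratio. Within it adjustment costs essentially no power and keeps type I error near 5%. Any further gain from gestation or age was not estimated and is not claimed.

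**What to change.** Amend the Statistical tests section, with a date before unblinding:

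- **Primary analysis:** logistic regression of miscarriage before 20 weeks on treatment, fetal heart status at entry (seen, not seen, sac only), gestation at entry, and optionally age. Hospital may be added but is not needed for power.
- **Reported effect:** standardise the model to a marginal risk difference or risk ratio with 95% confidence interval, so that the outcome remains a percentage. State which p value is primary.
- **Supportive analysis:** the unadjusted chi-square test, on the same women.
- **Details to fix now:** the coding of heart status (including how one status is assigned in a multiple pregnancy, since these are eligible), the form of gestation in the model, and a rule for merging categories if one is very small.
- **Keep separate:** the exploratory logistic regression for predictors, labelled as such.

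The cost is a change of wording and somewhat more analysis work, mainly for the standardised estimate and its interval. The small downside is reliance on a prespecified model. No extra patients, visits or measurements are needed, and the sample size can stay as it is.

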Treatment will be stopped if the vaginal bleeding becomes severe and requires surgical intervention, or a diagnosis of silent miscarriage is confirmed upon a follow-up scan (i.e., the gestational sac or fetal pole fails to grow after 1 week, or there is no cardiac activity in a fetal pole with crown-rump length of ≥7 mm). If the patient has a spontaneous miscarriage, the tissue mass passed or obtained after medical or surgical evacuation will be sent for histology and karyotyping by quantitative fluorescence-polymerase chain reaction (QF‐PCR) or the array comparative genomic hybridization method. QF-PCR, which is a simple and cheap method, will first be used to exclude common aneuploidy of chromosomes 13, 18, 21 and XY. The array comparative genomic hybridization method will be employed in those with negative QF-PCR results to confirm or exclude aneuploidy.

The primary outcome is the percentage of miscarriages before 20 weeks of gestation. The secondary outcomes are the live birth rate; the proportion of heavy vaginal bleeding or severe abdominal pain requiring surgical intervention (after 20 weeks); and obstetric complications including antepartum hemorrhage, placenta previa, pregnancy-induced hypertension, intrauterine death, congenital abnormality, preterm labor, and low birth weight at term. The birth weight, gestational age at delivery and apgar score are also included. The definitions of the obstetric complications are as follows:Antepartum hemorrhage: any vaginal bleeding during pregnancy from the 24th week of gestational age to termPlacenta previa: placenta inserting partially or wholly in the lower uterine segment, diagnosed by antenatal ultrasound at the second and third trimestersPregnancy-induced hypertension: development of new-onset hypertension (blood pressure persistently 140/90 mmHg or higher on two occasions at least 4 hours apart) during pregnancy after 20 weeks’ gestation, labor or the puerperium in a previously normotensive non-proteinuric womenIntrauterine death: fetal death in utero after 24 weeks’ gestationPreterm labor: any premature spontaneous delivery from 24 weeks’ to 36 weeks’ gestationLow birth weight at term: baby born with birth weight less than 2500 g at or after 37 weeks’ gestation

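### The planned subgroup that drops women with an abnormal karyotype in the abortus removes only outcome events after randomisation, so randomisation does not protect its comparison

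*Protocol article*

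**What the plan says.** The primary outcome is defined in the protocol article under Treatment of subjects: "The primary outcome is the percentage of miscarriages before 20 weeks of gestation". Under Statistical tests it "will be analyzed with the chi-square test", and the analyses are run "using intention-to-treat and per protocol analyses".

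The same section then announces: "Subgroup analysis for the primary outcome will be done with regard to gravida, gestation at presentation". The list continues with subchorionic hematoma and ends with an analysis "after exclusion of those with an abnormal karotype in the abortus". One significance rule follows for everything: "A *p* value <0.05 will be considered as statistically significant".

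Who has a karyotype is settled under Treatment of subjects. If a woman miscarries spontaneously, "the tissue mass passed or obtained after medical or surgical evacuation will be sent for histology and karyotyping". Testing is in two steps, a PCR screen for common aneuploidies and then an array method if the screen is negative. No karyotyping is described for pregnancies that continue. The article does not call the karyotype analysis exploratory.

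**The concern.** Gravida and gestation at presentation are known at entry, so the arms within such a subgroup remain randomised groups. The karyotype exclusion is different in three ways:

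- Everyone it removes has miscarried. In effect it takes primary-outcome events out of the numerator and the denominator and can never take out a non-event.
- It acts on information seen only after treatment has begun.
- It acts only where tissue was recovered and gave a result. An abnormal loss without tissue stays in as an event, and an abnormal pregnancy still continuing at 20 weeks stays in as a success.

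What remains is no longer the randomised comparison. At stake is how a result in apparently chromosomally normal pregnancies would be read. The Background names embryonic chromosomal abnormality as the commonest first-trimester cause of miscarriage, so the exclusion may remove a large share of events. If the share removed differs by arm for reasons unrelated to benefit, the analysis can suggest a benefit or a harm that is not there, or hide a real one.

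**Working it through.** **The plan's own figure.** Sample size estimation gives 14.8% versus 27.1%, power 80%, type I error 0.05, 171 per group. With pooled variance, two-sided, no continuity correction, and mean rate 0.2095:

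n = [1.96·√(2·0.2095·0.7905) + 0.8416·√(0.148·0.852 + 0.271·0.729)]² / 0.123² = (1.128 + 0.479)² / 0.01513 ≈ 171.

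The figure reproduces, and nothing below changes it.

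**Inputs for the check.** From the documents: 200 per arm and the 27.1% control rate. Assumed, because the documents give no values: an alternative risk of 20%, the share a of miscarriages with an abnormal karyotype, and the probability d that an abnormal karyotype is detected. The simulations covered a from 40% to 70%.

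**Formula.** With true miscarriage risk p, the risk left after the exclusion is

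r(d) = p(1 − a·d) / (1 − p·a·d).

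**Step 1: equal detection, no treatment effect.** Both arms have the same r(d), so the risk ratio (RR) is 1.00 whatever d is. In simulation (200,000 replicates, two-sided chi-square at 0.05), rejection stayed at 4.9–5.1% for risks of 14.8%, 20% and 27.1% and every abnormal share tried.

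**Step 2: unequal detection, no treatment effect.**

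For p = 20%, a = 60%, each arm has 40 losses, 24 of them abnormal.
- 80% versus 70%: (40 − 19.2)/(200 − 19.2) = 20.8/180.8 = 11.5%; (40 − 16.8)/(200 − 16.8) = 23.2/183.2 = 12.7%; RR 0.91.
- 90% versus 50%: 18.4/178.4 = 10.3%; 28/188 = 14.9%; RR 0.69.

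For p = 27.1%, a = 50%:
- 80% versus 70%: 0.1626/0.8916 = 18.2%; 0.17615/0.90515 = 19.5%; RR 0.94.
- 90% versus 50%: 0.14905/0.87805 = 17.0%; 0.20325/0.93225 = 21.8%; RR 0.78.

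| Detection, dydrogesterone vs placebo | RR (rejection), p = 20%, a = 60% | RR (rejection), p = 27.1%, a = 50% |
|---|---|---|
| 80% vs 70% | 0.91 (6.2%) | 0.94 (6.0%) |
| 90% vs 70% | 0.81 (10.6%) | 0.87 (9.3%) |
| 90% vs 50% | 0.69 (26%) | 0.78 (21%) |
| 50% vs 90% | 1.44 (26%) | 1.28 (21%) |

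The last row shows that reversing the imbalance reverses the direction.

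**Step 3: treatment only carries abnormal pregnancies past 20 weeks.** Take p = 27.1%, a = 50%, full detection and no effect on normal pregnancies. The placebo arm shows 0.1355/(1 − 0.1355) = 15.7%. If half the abnormal losses are carried, the treated arm shows 0.1355/(1 − 0.06775) = 14.5%, RR 0.93. If all are carried it shows 0.1355/1, RR 0.86. For a = 50–60%, carrying 25–50% gives RR 0.91–0.96 with rejection of about 5% or less; carrying all gives 0.84–0.86 with about 8–9%.

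**Step 4: does keeping the denominator cure it?** It cures step 3, since 0.1355 over all women in each arm gives RR 1.00. It does not cure step 2. With p = 20%, a = 60% and recovery of 90% versus 50%, the expected counts per 200 women are:

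| | Normal | Abnormal | Not obtained |
|---|---|---|---|
| Dydrogesterone | 14.4 | 21.6 | 4 |
| Placebo | 8 | 12 | 20 |

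- Observed normal loss only: 14.4/200 versus 8/200, RR 1.80. At 80% versus 70% it is 12.8 versus 11.2, RR 1.14.
- Normal or not obtained: 18.4/200 versus 28/200, RR 0.66.
- Unknowns filled in by each arm's observed 40% normal share: 14.4 + 1.6 = 16 versus 8 + 8 = 16, RR 1.00.
- Extreme bounds: 14.4/28 = 0.51 to 18.4/8 = 2.30.

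**The case against.** The strongest reply is that an outcome-dependent exclusion does not create an effect by itself. Embryonic karyotype is largely set before randomisation, both arms follow one karyotyping rule, clinicians and patients are blinded, and under equal detection the test keeps its 5% level (step 1). All of that stands. A reader might infer that the analysis produces a false effect merely because of how it is built; the documents do not support that. A further condition is needed, and they neither state nor exclude it.

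The condition is not far-fetched. The Background credits progesterone with keeping the myometrium quiescent, and the article foresees both tissue passed spontaneously and tissue from evacuation. Blinding guards against staff treating the arms differently, but not against a drug effect on how a loss presents. That remains a possibility, not a finding.

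The sizes may also be challenged. The 90% versus 50% split is an assumed extreme for a double-blind trial, and a ten-point gap moves rejection only to about 6%. That stands too.

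Finally, it may be said that an article leaves such detail to the full plan. Labelling and missing-karyotype rules alone could be left there. The exclusion itself, however, is stated in the article and set beside subgroups defined at entry.

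**Conclusion.** The point holds as a conditional one. The karyotype analysis is not a baseline subgroup, and its comparison is not protected by randomisation. Under the null it is unbiased if karyotype ascertainment is equal by arm and treatment does not alter the loss of abnormal pregnancies; otherwise it can err in either direction. Under the assumed inputs the bias is small for a modest imbalance (RR about 0.91–0.94 at 80% versus 70%) and substantial only for an extreme one (about 0.69–0.78 at 90% versus 50%). Abnormal share and recovery rates are assumptions throughout.

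A reader might also infer that the trial's main result is compromised. It is not: the primary chi-square comparison does not use this exclusion, and the sample size is unaffected. This is a point that should be fixed, not one that blocks the trial.

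**What to change.** Take the karyotype exclusion out of the subgroup list and replace it with an analysis labelled exploratory:

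1. Keep every randomised woman with a known primary outcome in the denominator of her assigned arm.
2. Classify each miscarriage before 20 weeks as normal karyotype, abnormal karyotype or karyotype not obtained, and compare all three categories by arm.
3. Report karyotype availability among miscarriages by arm.
4. Base any comparison of normal-karyotype loss on multiple imputation of the unknown karyotypes, with best- and worst-case bounds beside it. This belongs in the main replacement analysis, because step 4 of the working shows that the full denominator alone leaves differential ascertainment uncured. The imputation assumes that, within arm and given the recorded covariates, availability does not depend on the karyotype; the bounds show how much rests on that.

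No new data are needed, and the article already foresees multiple imputation for missing responses. The cost is a little more analysis work and a result less simple than a single subgroup risk ratio. The 171 per group and the 400 recruited stay as they are.

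### The named missing-outcome stress test applies one rule to both arms, so when loss is about equal it cannot show loss whose link to outcome differs by arm

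*Protocol article*

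**What the plan says.** Under Statistical tests, the protocol article states: "All statistical analyses will be performed using IBM SPSS software using intention-to-treat and per protocol analyses". The primary endpoint is binary, miscarriage before 20 weeks, and "The primary outcome, the percentage of miscarriage before 20 weeks of gestation, will be analyzed with the chi-square test". On missing outcomes it then says: "Women with missing primary outcome data will not be included in the primary analysis". It openly calls this a risk of bias and promises sensitivity analyses, "including the assumption that all women lost to follow-up have miscarriages before 20 weeks", with multiple imputation as a further one. Women are to be followed even after a protocol violation, and on the amount of loss it says: "It is thus anticipated that missing data will be minimal".

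Under Sample size estimation, "a sample size of 171 per group is needed to achieve a power of 80 % with a type I error of 0.05", based on pooled miscarriage rates of 27/182 (14.8%) and 42/155 (27.1%). Then: "To allow for drop out, we plan to recruit 400 subjects in total with 200 patients in each arm". No dropout percentage is given.

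**The concern.** Two features combine. First, the primary comparison covers only women whose outcome is known, although the analysis is called intention-to-treat. It is therefore protected by randomisation only if loss is unrelated to outcome or related to it in the same way in both arms. Second, the single stress test that is spelled out assigns the same fate to every lost woman, whichever arm she was in. If the two arms lose similar numbers, it adds similar numbers of events to each and says little about the harmful case, in which lost women fare differently on dydrogesterone than on placebo. Multiple imputation in its usual missing-at-random form does not probe that case either, and the article states no other assumption for it.

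At stake is the robustness statement on the primary outcome. A result could be reported as withstanding missing data although the checks named did not test the pattern that would undo it.

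**Working it through.** **Inputs.** Design rates 14.8% and 27.1%, 171 per group, 200 randomised per arm (Sample size estimation); 1:1 allocation (Treatment of subjects); chi-square test, p<0.05 (Statistical tests). The numbers lost are assumptions, since the article gives no loss rate. Observed women are set at the design rates, using the unrounded fractions 27/182 and 42/155, and p values come from the chi-square test without continuity correction.

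**The plan's own figure.** With p1=0.148, p2=0.271, mean 0.2095, two-sided 5% and 80% power:

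n = [1.96·√(2·0.2095·0.7905) + 0.842·√(0.148·0.852 + 0.271·0.729)]² / 0.123² = 170.7, rounded up to 171.

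The stated 171 reproduces. The step to 200 leaves room for 1 − 171/200 = 14.5%, or 29 women per arm.

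**Why the named scenario is limited under equal loss.** Let N be randomised per arm, m lost in each arm, and a and b the observed events on treatment and control.

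- Complete-case difference: (a − b)/(N − m).
- All lost counted as miscarriages: (a + m)/N − (b + m)/N = (a − b)/N, which is the complete-case difference times (N − m)/N. The sign cannot change.
- Arm-specific worst case (all lost treated women miscarry, no lost controls do): (a + m − b)/N. The sign changes once m exceeds b − a.

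**10 lost per arm (5%).**

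| Analysis | Dydrogesterone | Placebo | Difference | p |
|---|---|---|---|---|
| Complete-case | 28/190 (14.7%) | 51/190 (26.8%) | −12.1 points | 0.004 |
| All lost miscarried | 38/200 (19.0%) | 61/200 (30.5%) | −11.5 points | 0.008 |
| Arm-specific worst case | 38/200 (19.0%) | 51/200 (25.5%) | −6.5 points | 0.12 |

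**29 lost per arm (14.5%).**

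| Analysis | Dydrogesterone | Placebo | Difference | p |
|---|---|---|---|---|
| Complete-case | 25/171 (14.6%) | 46/171 (26.9%) | −12.3 points | 0.005 |
| All lost miscarried | 54/200 (27.0%) | 75/200 (37.5%) | −10.5 points | 0.025 |
| Arm-specific worst case | 54/200 (27.0%) | 46/200 (23.0%) | +4.0 points | 0.36 |

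At smaller equal losses the worst case stays significant: p=0.015 with 4 lost per arm (2%) and p=0.030 with 6 (3%).

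**A less extreme pattern.** Keep 29 lost per arm and let 8 of the 29 lost controls miscarry (28%, close to the design rate), so that control is (46 + 8)/200 = 54/200. With 12 of 29 lost treated women miscarrying, treatment is 37/200 and p=0.043. With 13 of 29 (45%) it is 38/200 and p=0.057. Significance is lost at 13.

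**Where the named scenario does react.**

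- Unequal numbers lost: 40 on treatment and 18 on control moves the result from p=0.007 (24/160 v 49/182) to p=0.75 (64/200 v 67/200). With 48 and 10 lost, the direction reverses (71/200 v 61/200, p=0.29).
- Equal loss, weaker result: 25/171 v 43/171, p=0.015, becomes 54/200 v 72/200, p=0.053.

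**The case against.** A reader might infer that the named scenario is useless against informative loss. The documents do not support that. It responds strongly when the arms lose different numbers, and it can remove significance from a weaker result even under equal loss, as the last two examples show. It also matches the most obvious mechanism, in which women who miscarry do not come back.

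A reader might also infer that the plan budgets for 14.5% missing outcomes and so contradicts its own expectation of minimal missing data. That goes too far. The rate is derived, 200 may simply be a round number, and stopping treatment need not mean a missing outcome because follow-up continues. The section on treatment of subjects describes active tracing: consent at entry to retrieve pregnancy data, electronic records for public-hospital deliveries, and letters to private obstetricians. The article also discloses the bias risk, plans multiple imputation, and leaves its list of sensitivity analyses open. Complete-case with sensitivity analyses is a conventional choice.

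The worst case itself is extreme, and in a trial that blinds clinicians and patients there is no particular reason to expect it. Even the milder tipping point needs lost treated women to miscarry at 45%, about three times the 14.6% seen in those retained.

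All of this stands and limits the point. What it does not supply is an analysis in which the assumed outcome of lost women differs by arm. The blind spot also appears at 5% loss, so it does not depend on the derived 14.5%.

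**Conclusion.** The point holds in a narrow form. The primary analysis is complete-case under an intention-to-treat label, and neither named check examines outcome-related loss that differs by arm when the numbers lost are about equal. At the design rates, the gap between the plan's scenario and the arm-specific worst case is p=0.008 against p=0.12 with 10 lost per arm, and p=0.025 against a reversed direction with 29 lost per arm. These figures assume equal loss, retained women at the design rates and an uncorrected chi-square test. The worst case marks a bound and is not a forecast. If loss stays at 3% or below in each arm, even that bound keeps significance at these rates and the matter has little consequence. The statement about multiple imputation assumes its standard missing-at-random form, since the article names no assumption. The documents do not show that the primary analysis must be replaced: making multiple imputation primary would be a debatable trade and would not by itself address arm-specific loss.

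**What to change.** Complete-case may remain the primary analysis, but describe its population as randomised women with an observed primary outcome. Keep multiple imputation as a sensitivity analysis, and keep the scenario in which all lost women miscarried. Add a tipping-point analysis that varies the assumed miscarriage rate among lost women separately in each arm, includes the arm-specific worst case, and reports the combinations at which significance and direction change.

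The cost is a few lines of plan text and a little programming; no new data are needed. The downside is that the robustness statement may turn out less favourable than under the present checks.
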